### Provisions for post-trial care

Participants’ GP are informed about the end of trial participation at 52 weeks. Any indication of worsening depression symptoms, increased risk or need for a higher level of clinical care prompted by participant response at outcome measurement is communicated to the GP as per risk protocol. This applies at 52 weeks.

### Data collection

Participants will be asked to complete an ADEPT-2 follow-up questionnaire at 16, 32 and 52 weeks post randomisation. Participants will be asked to complete the questionnaires online and will receive a secure online link at the appropriate time points. Alternative methods preferred by the participant will be considered and facilitated where feasible (eg, by video call (using Sponsor/NHS-approved video-conferencing tools), postal hard copy, face-to-face or telephone). If the participant requires assistance to complete the questionnaires, the research team will aim to try and make all reasonable adjustments requested by the participant to facilitate this. Similarly, a carer/family member or friend can provide support, but they will be advised not to answer any questions on behalf of the participant.

Carers taking part in the carer substudy will be asked to complete online follow-up questionnaires at 16 and 52 weeks after the participant they care for was randomised in the main trial.

### Data management

Data from all participants will be collected and retained in accordance with the UK Data Protection Act 2018 and the UK General Data Protection Regulation 2018 (GDPR). All trial participants will be allocated a unique study ID number during the screening process, which will remain assigned to them. Data from all participants will be captured electronically via REDCap. However, where electronic data collection is not possible, equivalent paper documents will become the source data. Personal identifiers will be kept in a secure database that is only accessible from within the UniBristol firewall. Anonymised clinical data will be held on a separate server and will be linked by a participant ID.

The University of Bristol and University of Bath are joint data controllers for the ADEPT-2 trial. Data will be held at the University of Bristol and will conform to the University of Bristol Data Security Policy and in compliance with the UK GDPR, alongside the Data Protection Act 2018. Secure email links, econsent, automated reminders.

Data will be retained for at least 5 years after the end of the trial, and at the end of the archiving period, will be destroyed by confidential means with the exception of a final data set which will be made available for data-sharing purposes.

### Sample size

99 participants in each of the GSH and TAU groups and returning the primary outcome measure will allow a minimum clinically important difference of 0.4 SD^40^ on the primary outcome (approximately four points on the BDI-II scale, a 13% reduction on the mean baseline score of 31 seen in the external pilot study participants) to be detected with 90% power at the 5% significance level, in an analysis adjusting for the baseline measure of the primary outcome and assuming a correlation of 0.5 between baseline and 16-week assessments. We set a sample size target of 248 participants (124 in each group) to allow 90% power to be achieved with up to 20% of primary outcome measurements being missing.

### Statistical analysis

A detailed statistical analysis plan will be written prior to the trial data being released for analysis and will be made publicly available. The primary analysis will follow the intention-to-treat analysis principle, comparing BDI-II responses at the 16-week assessment point between the groups as allocated. The treatment effect on the primary outcome will be estimated by a linear regression model with covariates including the baseline BDI-II measure, trial centre, current prescription of antidepressant medication and treatment group allocation. The treatment effect will be estimated as the coefficient of the treatment group allocation covariate, with a 95% CI and p value. This approach will be adapted to the secondary measures. Sensitivity analyses will explore the potential impact of any missing primary outcome data. Any subgroup analyses will be prespecified in the statistical analysis plan. No interim analyses are planned.

To investigate the correlation between attending sessions and the primary outcome response, we will present summary statistics for the 16-week BDI-II for the intervention group participants who attend 0, 1–5 and 6 or more sessions. A sensitivity analysis will repeat the primary analysis on a complier average causal effect basis, comparing intervention group participants attending one or more sessions against the estimated outcome of the comparable participants allocated to the comparison group (ie, those comparison group participants who would have attended one or more sessions had they instead been allocated to the intervention).

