### Trial intervention/randomised treatments

#### Guided self-help

The GSH intervention is based on the principles of BA, the recommended treatment model for low-intensity CBT for depression. BA^24^ encourages people to become more aware of the range of behaviours and situations associated with different moods and use this information to make changes in line with their individual goals through activity scheduling. Doing more of what makes you feel good is the key mechanism.

Participants randomised to GSH are provided with a booklet (electronic and print/pdf) containing informational materials for nine topics. They are invited to attend nine individual meetings with a therapist guide (hereon in called a GSH coach) ordinarily held at weekly intervals. GSH sessions can last up to 45 min (except for the first session which can last up to 90 min). Sessions are held online using the NHS-approved platform for that service/region. If participant preference is for in-person attendance, where feasible this will be facilitated. During GSH sessions, the materials are reviewed and discussed on screen with collaborative work and annotation to encourage personalisation of the electronic and/or print versions of the booklet according to individual preference. Between session tasks are suggested to consolidate the treatment principles, and this is checked for completion and quality by the coach at the next appointment.

GSH coaches are ordinarily graduate-level psychological practitioners or other mental health professionals with foundation knowledge of cognitive behavioural principles. GSH coaches receive 15 hours of training and an accompanying coach manual. GSH coaches attend weekly group supervision.

The GSH intervention was developed for the feasibility study and refined on the basis of participant feedback. Additional visual images were commissioned from an autistic graphic artist to improve the accessibility and appearance of the materials.

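### Sample size and stated primary regression make no allowance for clustering by coach in the GSH arm, so 90% power and 5% error hold only if the coach ICC is zero

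*Protocol article*

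**What the plan says.** All references are to the Protocol article.

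- **Guided self-help.** On the GSH arm: "They are invited to attend nine individual meetings with a therapist guide". The guide is the GSH coach. Coaches work from a manual after 15 hours of training and are supervised weekly in groups.
- **Treatment as usual.** TAU is unconstrained: participants are signposted to NHS services and their GP is told of the allocation. No trial coach is involved.
- **Sample size.** The basis is "99 participants in each of the GSH and TAU groups and returning the primary outcome measure", a difference of 0.4 SD, and "assuming a correlation of 0.5 between baseline and 16-week assessments". The difference is "to be detected with 90% power at the 5% significance level, in an analysis adjusting for the baseline measure of the primary outcome". The target of 248 allows for 20% missing primary outcomes. No ICC, coach caseload or design effect appears.
- **Statistical analysis.** The primary model is: "The treatment effect on the primary outcome will be estimated by a linear regression model with covariates including the baseline BDI-II measure, trial centre", plus antidepressant prescription and treatment group. There is no coach term or robust variance. The sensitivity analyses named concern missing data and the complier average causal effect.

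**The concern.** Participants who share a coach may have correlated outcomes, because coaches can differ in skill, alliance and adherence. The protocol itself measures alliance and adherence. The correlation can arise in one arm only, which makes this a partially nested design. A centre covariate common to both arms cannot absorb a coach effect confined to GSH.

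If the correlation is positive, the GSH mean is less precise than an analysis of independent observations assumes. The planned p value and confidence interval for the primary outcome would then be over-precise, and an analysis that corrects this would have less than the stated 90% power.

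**Working it through.** **Inputs from the Sample size section.** Difference 0.4 SD; baseline to 16-week correlation 0.5, so the residual variance factor is 1 − 0.5² = 0.75; power 90%; significance level 5%, taken as two-sided (not stated, but it reproduces the figure); 99 analysed per arm.

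**Step 1: reproduce the plan's figure.**
n per arm = 2(1.96 + 1.2816)² / 0.4² × 0.75 = 98.5, so 99.
99 / 0.8 = 123.75, so 124 per arm and 248 in total.
Both figures reproduce exactly under independence, so no design effect is hidden in them.

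**Step 2: assumed inputs.** The article gives neither the coach ICC (ρ, on the baseline-adjusted residual scale) nor the number of coaches (K). I take ρ of 0.02 and 0.05, and K of 6, 10, 12 and 24.

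**Step 3: formulas (normal approximation).**
- Caseload m = 99/K; design effect in the GSH arm DE = 1 + (m − 1)ρ.
- Standard error (SE) assumed by the plan: SE₀ = √(0.75 × 2/99) = 0.1231.
- True standard error: SE₁ = √(0.75 × (1 + DE)/99).
- Type I error of the planned regression: 2[1 − Φ(1.96 × SE₀/SE₁)].
- Power of a coach-adjusted analysis: Φ(0.4/SE₁ − 1.96).
- Probability that the planned regression rejects at 0.4 SD: Φ((0.4 − 1.96 × SE₀)/SE₁).

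Worked case, K = 10 and ρ = 0.05: m = 9.9; DE = 1 + 8.9 × 0.05 = 1.445; SE₁ = √(0.75 × 2.445/99) = 0.1361; SE₁/SE₀ = 1.106. Type I error is 7.6%, adjusted power is Φ(2.939 − 1.96) = 83.6%, and planned-model rejection is Φ(0.1587/0.1361) = 87.8%.

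| Coaches | ICC | DE | SE₁/SE₀ | Type I error, planned model | Power, coach-adjusted | Rejection at 0.4 SD, planned model |
|---|---|---|---|---|---|---|
| any | 0 | 1.000 | 1.00 | 5.0% | 90.1% | 90.1% |
| 6 | 0.05 | 1.775 | 1.18 | 9.6% | 78.8% | 86.3% |
| 10 | 0.02 | 1.178 | 1.04 | 6.0% | 87.6% | 89.2% |
| 10 | 0.05 | 1.445 | 1.11 | 7.6% | 83.6% | 87.8% |
| 12 | 0.02 | 1.145 | 1.04 | 5.8% | 88.1% | 89.3% |
| 12 | 0.05 | 1.363 | 1.09 | 7.1% | 84.8% | 88.2% |
| 24 | 0.02 | 1.063 | 1.02 | 5.4% | 89.3% | 89.8% |

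**Step 4: does the centre covariate help?** A simulation fitted the stated regression on baseline score, centre and arm, with coaches nested in six centres (antidepressant prescription was not simulated). At ICC 0.02 and 0.05, type I error was about 6.9% and 9.4% with 6 coaches, and 5.8% and 7.3% with 12. These agree with the formulas, so adjusting for centre does not remove the problem.

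**The case against.** **The SAP may deal with it.** The section defers to a SAP that is not shown, its covariate list is not exhaustive, and the article condenses a fuller protocol. A clustering analysis could sit in either document. This stands in part. But a random effect in one arm is a different model from the linear regression named here, and no SAP can restore power lost by a sample size set without a design effect.

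**The effect may be small.** This stands. The intervention is manualised and supervised, so a low ICC is plausible, though not established. With ICC 0.01 and 10 or more coaches, power stays within about one point of 90% and type I error is 5.1 to 5.5%.

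**Stronger readings that the article does not support.**
- A reader might infer that the stated power and error rate certainly fail. They fail only if the ICC is positive, and materially only if caseloads are large enough.
- A reader might take the 10 coaches in the Qualitative study section as the number in the trial. That is an interview target.
- A reader might quote 79% as the power of the planned analysis. It belongs to a coach-adjusted test; the planned regression would reject about 86% of the time in that setting, but with a type I error of 9.6%.
- A reader might say that the error favours GSH. The excess type I error is two-sided and under the null falls equally in both directions.

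**Conclusion.** The point holds in conditional form. The sample size arithmetic is correct on its own inputs, but those inputs and the named primary model assume independence that the delivery of GSH puts in doubt. With any positive coach ICC, the stated model gives too small a standard error. The 90% power holds only with no coach clustering.

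Over the assumed settings with 6 to 12 coaches and ICC 0.02 to 0.05, the planned regression has type I error of about 6 to 10% and rejects at 0.4 SD with about 86 to 89% probability; a coach-adjusted analysis has about 79 to 88% power. With 24 or more coaches and ICC 0.02 or less, the effect is negligible. All of this rests on equal caseloads, 99 analysed per arm, a normal approximation, and values for the ICC and number of coaches that the article does not give. It is worth correcting before analysis; whether it is serious depends on the actual number of coaches.

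**What to change.** Before data release:

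1. Prespecify as primary a partially nested mixed model with the same covariates, a random coach intercept in the GSH arm only, arm-specific residual variances, and small-sample degrees of freedom (Satterthwaite or Kenward-Roger).
2. State how GSH participants who attend no session enter the model: by assigned coach, or as singleton clusters if none was assigned.
3. Keep the plain linear regression as a sensitivity analysis, and report the estimated coach ICC.
4. Confirm that coach identity is recorded for each GSH participant. The article mentions therapist records but does not list this field.
5. Restate the Sample size paragraph to say that 90% power assumes no coach clustering, and give the power over a stated ICC range at the actual number of coaches.

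The cost is wording and one different model. Valid inference needs no extra recruitment. Restoring 90% power would: with 10 coaches at the same caseload, about 270 randomised at ICC 0.02 and 304 at ICC 0.05. The proposal is therefore to disclose the lower power, not to enlarge the trial. The downside is a somewhat wider confidence interval and a lower stated power, noticeably lower if coaches are few. With few coaches the variance component is also poorly estimated, and small-sample degrees of freedom would reduce power below the normal-approximation figures above.

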### Health economic analysis

The primary cost-utility analysis will assess the cost-effectiveness of GSH compared with TAU at 52 weeks, from a societal perspective including the NHS, personal social services (PSS), personal expenses, voluntary services and productivity. A secondary analysis will restrict the perspective to that of the NHS and PSS to conform to the NICE reference case.^41^ Utility values will be estimated from EQ-5D-5L scores collected at baseline, 16, 32 and 52 weeks follow-up using the NICE-recommended approach at the time of analysis. QALYs will be estimated from utility scores using the area under the curve approach, adjusting for baseline utility.^42^

Intervention costs (including training, delivery and supervision) will be recorded in study records. All-cause resource use, including primary, community and secondary care, prescribed and over-the-counter medications, time off paid employment, social care contacts, travel for healthcare and charity support services, will be captured via participant-report at 16, 32 and 52 weeks follow-up.^38 43^ Resources will be valued using published unit costs for the most recent cost year available at the time of analysis.^44^,^47^ Given the 1-year study duration, discounting will not be conducted.

A predefined health economics analysis plan to guide analysis will be prepared and made publicly available. Missing data patterns will be reviewed and handled appropriately. Net monetary benefit statistics, and if appropriate incremental cost-effectiveness ratios, will be calculated to assess cost-effectiveness. Uncertainty will be explored through cost-effectiveness acceptability curves and one-way sensitivity analyses.

### Qualitative study

To examine the views and experiences of the intervention and the trial, we will conduct in-depth qualitative interviews with up to 60 trial participants and 10 GSH coaches. Topic guides will be used for all interviews, specific to those being interviewed, which can be found in the online supplemental information. Qualitative findings will identify factors that may impact on the intervention acceptability and effectiveness. All participants in the trial will be asked if they are willing to be contacted about taking part in an interview at the time of trial consent. Autistic adults who decline or withdraw from participation in the main trial will be approached as soon as possible about taking part in an interview. Trial participants will be approached about an interview after they have completed their 16-week follow-up questionnaire, and the therapists will be approached at 4 months. The qualitative researcher will contact the participants via the participants’ preferred contact method and confirm if they would like to take part in the interviews. All interviews will be conducted remotely (by telephone/video call) and with informed consent, interviews will be audio recorded. Purposive theoretical sampling will ensure diversity in demographic characteristics (eg, age; gender; ethnicity; and socioeconomic status). Sample size will be determined by the concept of ‘information power’,^48^ with continuous assessment of information within our sample regarding meeting trial objectives. Data will be analysed using a thematic approach,^49^ and will be conducted in parallel to data collection, with findings from early analysis informing later data collection in an iterative process.

### Trial management and oversight

The Bristol Trials Centre will be responsible for the day-to-day management of the trial, including the preparation of trial documents, training and monitoring of centres. The TMG, a core working group of staff, will oversee the trial and meet regularly to review milestones. The TMG report to the Trial Steering Committee (TSC). The TSC are an independent committee that make recommendations and key decisions during the trial. The Data Monitoring Committee (DMC) are an independent committee that assess the safety and efficacy of the trial’s interventions, monitor the trial’s overall conduct and protect its validity and credibility. Membership of the trial oversight committees is described in the Acknowledgements section.

### Safety

In accordance with Good Clinical Practice guidelines, adverse events and risk standardised operating procedures will be followed by all researchers and GSH coaches working on the trial. Adverse event data will be collected for the duration from randomisation to 52 weeks post randomisation. Adverse events will be identified during GSH appointments for participants allocated to GSH up to the 16-week follow-up, where adverse events will be detected via trial questionnaires (across GSH and TAU). The central and/or local research team will report any Adverse Events (AEs) that occur, should they become aware. The PI of each participating site is responsible for assessing all adverse events and categorising whether they are serious, expected and related. All suspected unexpected serious adverse reaction will be reported to the Sponsor, Research Ethics Committee (REC) and DMC.

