Each GSH session covers a key principle(s) which are delivered in a developmental sequence to consolidate learning. The first session is an orientation session to introduce GSH and understand an individual’s needs in respect of autism. Sessions 2–4 take a focus on noticing situations, different behaviours in situations, granularity of behaviours and rating positive feelings. Session 5 introduces activity scheduling, Session 6 the concept of meeting different levels of need, Sessions 7 and 8 consolidate and expand on activity scheduling and Session 9 comprises review, reflect and planning ahead.

The intervention is described in the feasibility study outcome paper.^20^

Consistent with low-intensity treatment recommendations, depression and anxiety symptoms are monitored weekly using the PHQ-9 and Generalised Anxiety Disorder Assessment (GAD-7).

GSH should commence 2 weeks post randomisation subject to individual availability of participant and coach. Attendance at ≥6 sessions of GSH will be considered an adequate treatment ‘dose’ as the main treatment principles have been introduced.

Delivery of the GSH intervention will be monitored by participants’ and GSH coaches’ recorded therapeutic alliance, using client and therapist versions of the Working Alliance Inventory-Short Revised (WAI-SR).^25^ This will be completed by GSH coaches and participants once within the first four sessions and once within the second four sessions at the same time as goal attainment measurement. Adherence to GSH content will be measured through a scale specific to the manual identifying key elements of therapy for each session. Therapist coaches will complete a self-rating of adherence to content for each session using this scale. Two GSH sessions, randomly allocated, will be audio recorded. 20% of these recordings will be randomly sampled to validate the therapist self-rating of adherence. ‘Intervention receipt’ will be monitored through therapist records of participants’ completed exercises and homework activity, ease of delivery and client engagement with the materials.

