### Major protocol amendments

The current protocol is V.3.0, 12 August 2024. The key change from V.1.0 was the addition of a telephone call 2 weeks post randomisation for TAU participants and the collection of information about possible Attention Deficit Hyperactivity Disorder (ADHD) and presence of an intellectual disability at baseline to characterise the sample further. The key change from V.2.0 was to clarify and correct errors in table 3, and to update the study timelines in line with a contract extension. The full protocol is available from the National Institute for Health and Care Research (NIHR) Journals web page (https://www.fundingawards.nihr.ac.uk/award/NIHR132343).

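### Up to week 16 adverse events are identified at coach sessions in the GSH arm only, so all-source counts by arm would tend to show more events in GSH even if true risks were equal

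*Protocol article*

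**What the plan says.** The Safety section sets the collection window: "Adverse event data will be collected for the duration from randomisation to 52 weeks post randomisation". Within it, three routes are described.

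- **GSH arm only, to week 16:** "Adverse events will be identified during GSH appointments for participants allocated to GSH up to the 16-week follow-up".
- **Both arms:** "adverse events will be detected via trial questionnaires (across GSH and TAU". Under Data collection, the questionnaires after randomisation fall at 16, 32 and 52 weeks.
- **Passive, not limited to one arm:** "The central and/or local research team will report any Adverse Events (AEs) that occur, should they become aware".

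The Guided self-help section sets the amount of contact in the intervention arm: "They are invited to attend nine individual meetings with a therapist guide", ordinarily a week apart, during which "depression and anxiety symptoms are monitored weekly using the PHQ-9 and Generalised Anxiety Disorder Assessment (GAD-7". The Intervention withdrawal section relies on that session-by-session PHQ-9 as evidence of worsening.

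For TAU, the only scheduled contact mentioned before week 16 is in Major protocol amendments: the "addition of a telephone call 2 weeks post randomisation for TAU participants". Its purpose is not given. Table 1 has no adverse-event row, and the only measures it marks in weeks 1 to 15 belong to the intervention arm.

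Site principal investigators, who are not blinded, classify the events. The DMC assesses safety.

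**The concern.** A recorded adverse-event rate is the true rate multiplied by the chance that an event is noticed. If that chance differs by arm, a table of recorded events compares surveillance as well as safety. Here the extra opportunities all lie in GSH, so the expected distortion is an excess of recorded events in GSH.

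Two errors become possible. A harmless intervention may look as if it causes events in a depressed population in which suicide risk is a stated worry. Alternatively, a real excess may be dismissed as a result of closer contact, because nothing in the table lets the two be told apart. The DMC would face the same ambiguity during the trial. An analysis plan written later cannot repair this unless the source of each event was recorded when the event was collected.

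**Working it through.** **Figures in the plan.** The article states no adverse-event rate and no safety power, so there is no safety figure to reproduce. The sample size is not in dispute and is used below only for scale: 2 × (1.960 + 1.282)² × (1 − 0.5²) / 0.4² = 98.5, so 99 per group; 99 / 0.80 = 123.75, so 124 per group and 248 in all, as stated.

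**Step 1: scheduled detection opportunities, randomisation to week 16.**

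| | GSH | TAU |
|---|---|---|
| Coach sessions | up to 9 | 0 |
| Week-16 questionnaire | 1 | 1 |
| Total | up to 10 | 1 |
| Total if the week-2 call counts | up to 10 | 2 |

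Nine is a maximum. In the feasibility study (Background), 86% attended six sessions and 71% attended all nine. With six sessions the count is 7 against 1 or 2. After week 16 each arm has the same two questionnaires.

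**Step 2: direction.** Let *s* be the chance that an event is recorded by the routes open to both arms, *c* the added chance per session and *k* the number of sessions, treated as independent. Detection is *s* in TAU and 1 − (1 − *s*)(1 − *c*)^*k* in GSH. With equal true risk the expected ratio of recorded risks is

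R = [1 − (1 − *s*)(1 − *c*)^*k*] / *s*,

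which exceeds 1 whenever *c* > 0 and *s* < 1.

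**Step 3: size, on assumed values.** None of *s*, *c* or the 20% true risk is in the article; *k* of 6 to 9 follows the pilot attendance. The last two columns are expected participants with a recorded event out of 124.

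| *s* | *c* | *k* | GSH detection | R | GSH | TAU |
|---|---|---|---|---|---|---|
| 0.9 | 0.05 | 6 | 0.926 | 1.03 | 23.0 | 22.3 |
| 0.7 | 0.10 | 9 | 0.884 | 1.26 | 21.9 | 17.4 |
| 0.5 | 0.10 | 9 | 0.806 | 1.61 | 20.0 | 12.4 |
| 0.5 | 0.20 | 9 | 0.933 | 1.87 | 23.1 | 12.4 |

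The first and last rows are the extremes over *s* 0.5 to 0.9, *c* 0.05 to 0.20 and *k* 6 to 9.

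**Step 4: dilution over 52 weeks.** R applies to events up to week 16. If the event rate is constant and *s* does not change, the ratio of event counts over the whole window is (16R + 36) / 52. For R = 1.03 this is 1.01, for R = 1.26 it is 1.08, and for R = 1.87 it is 1.27.

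**Step 5: would a questionnaire-only comparison be clean?** Only with the right denominator. Pilot retention at 16 weeks was 86% in GSH and 54% in TAU. If that recurred and events were divided by all randomised, equal true risk and equal detection among responders would still give 0.86 / 0.54 = 1.59 against GSH. Dividing by responders removes this, provided that non-return is unrelated to having had an event.

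**The case against.** The strongest case against the point has four parts.

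- **No comparison is specified.** Neither the Safety nor the Statistical analysis section names a between-arm adverse-event test or a pooled table. A reader might infer that the trial has a planned safety comparison that is biased against GSH. The article does not support that. It fixes how events are collected, and the problem arises in any all-source table built on that rule.
- **Details may lie elsewhere.** The article refers to operating procedures, a full protocol and an analysis plan. A reader might infer that event sources are not recorded, but silence in an article does not show this. What is stated is the unequal ascertainment itself, and nothing else in the article removes it.
- **More contact is inherent in a coached intervention against unconstrained TAU.** This stands. Coaches cannot ignore what they see, and an independent DMC with unblinded reports can allow for known differences in contact. It can do so far better if it sees the source of each event.
- **A questionnaire-only rule has its own hazard.** This also stands. GSH participants may be withdrawn for worsening seen at sessions. If they then return no questionnaire, their events would drop out and harm could be hidden. The pilot's unequal retention adds to the worry, although vouchers have been introduced to counter it. The all-source and serious events must therefore stay visible.

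The wording of the Safety sentence is loose: the clause on questionnaires can be read as describing the 16-week follow-up or follow-up generally. On either reading, session-based detection is in GSH only.

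**Conclusion.** The point holds for the period from randomisation to week 16. Scheduled detection opportunities are up to 10 in GSH against 1 in TAU, or 2 with the week-2 call. Neither that call, which has no stated adverse-event purpose, nor the passive route makes the arms equal.

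The direction under equal true risk follows from the design. The size does not: the range of 1.03 to 1.87 rests wholly on assumed detection rates and on independent detection at each session, and the distortion is negligible if questionnaires capture nearly every event.

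Two stronger readings should be avoided. Counting contacts to week 52 gives 9 + 3 = 12 against 3 + 1 = 4, but this treats the call as an adverse-event check and obscures that the arms are alike after week 16. Quoting a ratio of about 1.6 as the expected bias picks one point from an assumed range.

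The primary outcome is unaffected. This should be put right because the comparison concerns safety and the remedy is cheap, not because a large bias has been shown.

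**What to change.** 1. Record the source of every adverse event: GSH session, questionnaire at 16, 32 or 52 weeks, telephone call, or other. If the full protocol or the event form already does this, the sponsor need only confirm it.
2. Make the main between-arm comparison of non-serious adverse events, in the final analysis and in DMC reports, the one based on the 16-, 32- and 52-week questionnaires, with questionnaire responders in each arm as denominators.
3. Beside it, show all-source events and all serious events by arm, split by source, with a statement that all-source counts before week 16 reflect unequal ascertainment.
4. Clarify the Safety sentence, and say whether the week-2 TAU call asks about adverse events.

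The cost is one data field and some wording in the analysis plan and the DMC report template. The like-for-like set will be smaller, will rely on recall over as much as 20 weeks (week 32 to week 52), and may be incomplete if questionnaire return differs by arm; return rates by arm should be shown with it. Serious-event reporting and clinical management do not change, and the sample size stays at 248.
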